**Secondary outcome measures**

All secondary outcome measures will be collected at baseline and 6-months post-hospital discharge

**Post-traumatic stress disorder:**

The PTSD Checklist-Civilian Version (PCL-C) is a validated, standardised self-reporting questionairre for PTSD comprising of 17 items that correspond to key PTSD symptoms[77]. Using a 5-point scale, participants are asked to indicate how much they have been bothered by these problems within the last month. (1= not at all; 5 = Extremely) PCL-C is rated by adding total scores.

**Anxiety and depression:** Hospital Anxiety and Depression Scale (HADS) is a 14-item, self-reported measure with 7-items relating to symptoms of anxiety and 7-items relating to depression[78]. Each item is scored from 0-3, providing categorical total scores for anxiety and depression. 0-7 = normal. 8-10 = borderline. 11-21 = abnormal.

**Cognitive function:** Montreal Cognitive Assessment (MoCA) is a validated tool, used to detect cogntive impairment[79]. MoCA is a 30-point test of short-term memory, visuospatial ability, executive function, attention, language, abstract reasoning and orientation. Scores range from 0-30. A score higher than 26 is considered to indicate normal cognitive function.

**Health Related Quality of Life:** EQ5D -5L comprises five quality-of-life dimensions; mobility, self-care, usual activities, pain/discomfort andanxiety/depression. Participants report levels ranging from ‘no problems’ to ‘extreme problems’.

**Resilience:** The Brief Resilience Scale is a validated measure of resilience. The capacity to recover from a traumatic event is dependent on mental processing of those trauma.

**Physical activity:** Patients will wear a wristband activity monitor following consent and at final assessment point, 6-months post-hospital discharge. The equipment has been validated for medical use and will be worn 24 hours per day for 7 consecutive days.

**Nutritional assessment:** The scored Council of Nutrition Appetite Questionnaire provides a validated assessment of appetite and predicted weight-loss and takes approximately 5-minutes to complete.

- 1. ***Additional data***

Hospital research staff will provide the following demographic and hospital admission information:

Age

Gender

Living arrangements

Postcode

Ethnicity

Employment status

Pre admission functional comorbidity index

ICU diagnosis

APACHE II score [81]

Duration of level 3 care

Duration of level 2 care

ICU and hospital length of stay

Days of ventilation

Sedation days

Episodes of delirium according to daily CAM-ICU measures[82]

|  | **Baseline** | **Weekly – starting within 12-weeks of hospital discharge** | **6-months post-hospital discharge** | **Post-study completion** |
| --- | --- | --- | --- | --- |
| **Demographics** | **X** |  |  |  |
| **Medical history** | **X** |  |  |  |
| **Admission data** | **X** |  |  |  |
| **Informed consent** | **X** |  |  |  |
| **PCL-5** | **X** |  | **X** |  |
| **HADS** | **X** |  | **X** |  |
| **Montreal Cognitive Assessment** | **X** |  | **X** |  |
| **EQ5D-5L** | **X** |  | **X** |  |
| **BRS** | **X** |  | **X** |  |
| **CNAQ** | **X** |  | **X** |  |
| **Activity monitor** | **X** |  | **X** |  |
| **EMDR R-TEP Intervention** |  | **X** |  |  |
| **SUDs** |  | **X** |  |  |
| **Post-session assessment** |  | **X** |  |  |
| **Semi-structured interview^*^** |  |  |  | **X** |

**Figure two: trial schedule of events**

^*^ Representative sample of particpants and staff

1. **Sample size**

This is a feasibility study, the results of which will be used to power a definitive study if appropriate. We anticipate a 25% mortality /loss to follow-up. A total of 26 patients will be recruited to this study, with estimated total of 18-20 patients completing the study.

1. **Process evaluation**

Qualitative, in-depth, semi-structured interviews will be conducted with patients enrolled in the trial and professionals involved in the delivery of the trial at completion. Patients from both arms of the study (up to 6) and professionals from participating sites (up to 6) will be interviewed. This will provide an opportunity for the research team to reflect on the experiences of patients and professionals, identifying barriers and facilitators to trial processes (professionals) and trial experiences (patients), in order to gain an in-depth understanding on process/relationships/communications that helped or hindered conduct of the trial.

Within the self-report questionnaire patients will be asked to indicate whether they can be contacted to participate in an interview. Interviews will be conducted by telephone. Interviews will be conducted by a researcher with experience in qualitative process evaluations. Encrypted audio recorders will be used.

1. **Safety considerations**

A number of systematic reviews have reported no adverse events attributable to EMDR (52-56). The intervention will be undertaken by suitably trained and experienced psychological practitioners from the NHS Intensive Psychology Therapy Service, Branksome Clinic in Poole. IPTS primarily provides a service to individuals with complex and severe, persistent psychopathologies. The service has an established and defined risk management and clinical governance structure.

All interventions will be delivered or supervised by [name], Consultant Clinical Psychologist, Head of Service and trial board member.

Online sessions will be compliant with Digital Approaches to therapy guidance from the British Psychological Society [72]and NHS Digital [74]. (These guidance contain expected standards relating to safeguarding, information governance, and GDPR.

Prior to starting the EMDR R-TEP therapy the psychological therapist will undertake a risk assessment process. They will discuss who is present with the participant, whether support is available and ensure that confidentiality is maintained. In addition, emergency numbers (GP and 999) will be made available.

Participants who exhibit symptoms of intrusion/ escalation will be treated according to the protocol unless it is determined that further treatment or escalation to emergency care may be necessary/ indicated. If further treatment is required, the most appropriate course of action and referral pathway will be decided on a case-by-case basis by the psychology team.

Only adverse events (see definitions below) which occur during the intervention phase of the trial will be documented. These will be graded according to CTCAE version 4.0. Medical judgement will be exercised to determine whether an AE is serious. AEs that are not serious according to the definitions below but may jeopardise the subject or may require intervention to prevent a SAE, should also be considered as serious and reported accordingly.

All serious adverse events (SAE) will be documented and reported to the trial sponsor at [[contact]](mailto:[contact]) within 24 hours of occurrence.

Any deviations from the planned protocol will be recorded and reported immediately to the trial sponsor at [[contact]](mailto:[contact]).

Complete the SAE/SUSAR form & email a scanned copy of the form with as many details as possible to the sponsor ([contact]) together with anonymised relevant treatment forms and investigation reports.
Or
Contact the Research Ethics Committee by phone for advice and then email a scanned copy of the completed SAE/SUSAR form.

The UHS team will notify the necessary REC of all SUSARs occurring during the trial within 15 days. All investigators will be informed of all SUSARs occurring throughout the trial.

Local investigators should report any SUSARs and /or SAEs as required by their Local Research Ethics Committee and/or Research & Development Office.

**Adverse Event (AE):** any untoward medical occurrence in a participant or clinical trial subject that does not necessarily have a causal relationship with trial treatment or participation.

**Serious Adverse Event (SAE):** any untoward medical occurrence or effect that at any dose:

- Results in death
- Is life-threatening – refers to an event in which the subject was at risk of death at the time of the event; it does not refer to an event which hypothetically might have caused death if it were more severe
- Requires hospitalisation, or prolongation of existing in participants’ hospitalisation
- Results in persistent or significant disability or incapacity

**Suspected Unexpected Serious Adverse Reaction (SUSAR):** any suspected adverse reaction related to the trial procedures that is both unexpected and serious.

1. **Data collection and confidentiality**

Demographic and baseline questionnaire data will be collected following consent. Research nurses at the recruiting site will contact the participants via telephone at 4-months post-hospital discharge (+/- 2-weeks). Participants will be invited to repeat the baseline questionnaires, which will be posted to them with a pre-paid envelope. If participants prefer, the questionnaires can be completed over the telephone. These data will be securely stored as paper case report forms at the recruiting site.

All entries must be clear, legible and concordant with Good Clinical Practice. The local Principle Investigator is responsible for accuracy of data. Participating staff must be listed on the signed delegation log.

Prior to commencing the online conversation the therapy team will reiterate the boundaries of confidentiality and ensure ongoing consent. The participant’s preference of Skype^TM^ or Zoom^TM^ will be used in accordance with NHS Digital guidance. The therapist will not record the videoconference, unless specifically asked to do so by the participant, in which case written consent will need to be attained and the recording will be treated as part of their medical record. As in any other consultation, the therapist will ensure GDPR compliance for data storage and processing according to NHS Digital standards. [74]

The CovEMERALD study team and participating sites will act concordant with the Medical Research Council’s Guidelines for Good Clinical Practice in Clinical Trials and Good Research Practice: Principles and Guidelines.

All staff will act to preserve patient confidentiality and will not disclose any information by which patients may be identified. Electronic copies of the CRF will be transferred using secure nhs.net email accounts, with data encrypted to ensure anonymity. All procedures for handling, storing, destroying and processing data will be compliant with the Data Protection Act 2018.

All trial documentation and data will be archived centrally by the Sponsor at the end of trial in a purpose designed facility for ten years in accordance with regulatory requirements. Access to these archives will be restricted to authorised personnel. Electronic data sets will be stored indefinitely.

1. **Withdrawal of patient consent**

Patients who consent to trial participation, consent to undertake the assessments, interventions, follow-up and data collection. Trial participants retain the right to withdraw consent to trial participation at any point. This decision will be respected and the trial sponsor will be notified in writing. Participants will be asked whether the study team may continue to use trial data previously collected. If this is denied, all trial data will be destroyed in accordance with GDPR and Good Clinical Practice. Details will be recorded in the patient’s medical notes and no further data collection will occur.

1. **Monitoring and trial oversight**

This protocol, patient information sheets, informed consent forms and additional trial related literature will be reviewed by a Research Ethics Committee for compliance with applicable clinical research regulations. Approval will be gained before study commencement.

Day to day management of CovEMERALD, including site set-up, training and urgent consideration of safety concerns, will be the joint responsibility of [name], [name] and [name], (Co-Investigators) with additional supervisory oversight from [name].

**Trial Management Group:** bi-monthly meetings to discuss trial progress, issues arising and related research. Members include [name], [name], [name], [name], [name] and patient representatives [name] and [name].

**Trial sponsorship:** CovEMERALD will be peer-reviewed by subject expert clinicians and sponsored by University Hospital Southampton NHS Foundation Trust. Protocol deviations / violations and serious breaches of GCP will be reported to the sponsor using [[contact]](mailto:[contact])

**Monitoring:** The CI and PIs will facilitate any local monitoring by the R&D quality manager, REC review and provide access to source data as required. Following any monitoring a report will be provided which will summarise the visit and documents, along with any findings. The CI will be responsible for ensuring that all findings are addressed appropriately. The study group will review all events in a timely manner. Additional monitoring will be scheduled where there is evidence of suspicion of non-compliance with the Study protocol.

1. **Ethics**

After HRA approval, and the site has confirmed capacity & capability to deliver the study. Each site will be activated before patients can be entered into the trial.

The trial will be conducted in accordance with the recommendations for physicians involved in research on human subjects adopted by the 18th World Medical Assembly, Helsinki 1964 as revised and recognised by governing laws and EU Directives. Each subject’s consent to participate in the trial should be obtained after a full explanation has been given of treatment options, including the conventional and generally accepted methods of treatment. The right of the subject to refuse to participate in the trial without giving reasons must be respected.

After the subject has entered the trial, the clinician may give alternative treatment to that specified in the protocol, at any stage, if they feel it to be in the best interest of the subject. However, reasons for doing so should be recorded and the subject will remain within the trial for the purpose of follow-up and data analysis according to the treatment option to which they have been allocated. Similarly, the subject remains free to withdraw at any time from protocol treatment and trial follow-up without giving reasons and without prejudicing their further treatment.

1. **Sponsorship**

University Hospital Southampton NHS Foundation Trust is acting as the sponsor for this trial. UHS Research and Development will ensure that all regulatory policies adhered to in line with GCP. Other delegated duties will be assigned to the NHS Trusts or others taking part in this trial by means of the site clinical trial agreement. Any trial protocol deviations/violations and breaches of Good Clinical Practice occurring at sites should be reported to [[contact]](mailto:[contact]) and the local R&D Office immediately. The sponsor will then advise of and/or undertake any corrective and preventative actions as required.

The trial may be subject to inspection and audit by University Hospital Southampton NHS Foundation Trust, as the Sponsor’s delegate and other regulatory bodies to ensure adherence to ICH GCP, UK Policy for Health and Social Care Research, applicable contracts/agreements and national regulations.

The sponsor of the project is University Hospital Southampton NHS Foundation Trust. For NHS sponsored research HSG (96) 48 reference no.2 refers. If there is negligent harm during the clinical project when the NHS body owes a duty of care to the person harmed, NHS Indemnity covers NHS staff, medical academic staff with honorary contracts, and those conducting the project. NHS Indemnity does not offer no-fault compensation and is unable to agree in advance to pay compensation for non-negligent harm. Ex-gratia payments may be considered in the case of a claim.

1. **Dissemination plan**

Results of this proposed feasibility study will be disseminated with the aim of demonstrating feasibility of the intervention. In addition we hope to stimulate enthusiasm for centres to participate in the intended future trial.

Four key audiences for dissemination have been identified: i) patients and public; ii) Intensive care staff, healthcare workers and potential future research delivery partners; iii) service delivery organisations and iv) academic and potential future research collaborators.

Dissemination activities will include but not be limited to:

- Publication in peer reviewed journal
- Feedback to PPI study focus group
- Feedback to study participants
- Presentations to local clinical teams and managers and commissioners
- Presentation at conferences attended by appropriate healthcare professionals

Authors will be the chief investigator, principal investigators and members of the research team, each individually named.

If appropriate workshops will be organised to bring together stakeholders to share and interpret the findings with the aim of contributing to future trial design.

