**Primary Outcome measure**

**Feasibility**

Hospital research staff will collect data on number of eligible patients from their ICU, number of eligible patients approached and number consented.

Therapy staff will collect data on adherence to the trial protocol and sessions attended.

Feasibility will be determined by:

- Recruitment of >30% of eligible patients approached
- Complete early EMDR intervention programme in 75% or more of trial participants
- Protocol adherence
- Incidence of attributable adverse events
- Outcome measures completed in 75% or more of trial participants

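### Section 11 limits adverse-event recording to an undefined intervention phase; read naturally, this omits non-serious events in controls and after therapy, and it does not match the rule for serious events

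*Protocol*

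**What the plan says.** Protocol section 11 (Safety considerations) sets the recording rule: "Only adverse events (see definitions below) which occur during the intervention phase of the trial will be documented". It defines an adverse event without regard to cause, as "any untoward medical occurrence in a participant or clinical trial subject that does not necessarily have a causal relationship with trial treatment or participation". The next paragraph of the same section has a different scope: "All serious adverse events (SAE) will be documented and reported to the trial sponsor", with the report due "within 24 hours of occurrence". For unexpected serious reactions the scope is the whole trial: "The UHS team will notify the necessary REC of all SUSARs occurring during the trial within 15 days".

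The feasibility criteria, in the synopsis and under Primary Outcome measure, include "Incidence of attributable adverse events". No window, arm or attribution method is attached. The Abstract also makes tolerability part of the primary outcome.

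The protocol does not say when the intervention phase starts or ends, or whether controls have one. Three places bear on it:

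- **Intervention section, group one:** controls receive usual care and take health problems to the usual services.
- **Intervention section, group two:** therapy counts as complete once distress is rated 0 or 1 after at least 2 sessions, and stops at 8 sessions at most.
- **Schedule of events (Figure two):** the weekly column contains only the EMDR sessions, the distress rating and a post-session assessment. No row is named for adverse events at any time point.

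**The concern.** The recording rule fixes what a primary feasibility criterion can contain. If recording stops with the last session, non-serious harm that emerges later, such as worsening distress short of an SAE, cannot enter the count. The recording time is also shortest for those who have the fewest sessions, including anyone who stops early because therapy is distressing.

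The second issue is attribution. Recent ICU survivors have many background events, and the protocol itself allows for 25% mortality or loss. Because an adverse event is defined regardless of cause, someone must judge which events are attributable. Without the same events recorded in controls over the same period, that judgement has no background rate to draw on. The protocol's own Background section (Early interventions) reports that psychological debriefing led to worse outcomes than control, so a comparison with controls has already revealed harm from an early psychological intervention.

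Third, sites need to know what to record. An SAE is a kind of adverse event, so a rule that starts with only and a rule that starts with all give different answers for a serious event in a control, or in a treated patient after therapy. The 24-hour limit runs from the event itself, which staff cannot meet for outpatients whose events they learn of later.

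**Working it through.** **Scopes side by side (all in section 11)**

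| Event | Period stated | Arm stated |
| --- | --- | --- |
| Adverse event | Intervention phase only; phase undefined | None |
| Serious adverse event | No limit | No limit |
| SUSAR | Throughout the trial | No limit |

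Only the intervention arm has sessions, and the weekly column of Figure two holds only session-related items. The natural reading of intervention phase is therefore first to last session in treated patients. This is an inference, since the protocol gives no definition.

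**Inputs**

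- Sessions: 2 to 8, weekly (Appendix 2, When and how much).
- First appointment: within 12 weeks of discharge, so week 0 to 12 (Intervention section).
- Final assessment: 6 months after discharge (Secondary outcome measures; Figure two), which is 26.1 weeks.
- Allocation: 13 per arm (Lay summary).

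**Share of time covered**

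The protocol states no coverage figure to reproduce. Last session week = start week + (sessions − 1). Coverage = (sessions − 1) / (26.1 − start week).

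| Start week | Sessions | Last session week | Coverage to 6 months | Weeks not covered |
| --- | --- | --- | --- | --- |
| 0 | 2 | 1 | 1/26.1 = 3.8% | 25.1 |
| 0 | 8 | 7 | 7/26.1 = 26.8% | 19.1 |
| 12 | 2 | 13 | 1/14.1 = 7.1% | 13.1 |
| 12 | 8 | 19 | 7/14.1 = 49.6% | 7.1 |

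On the natural reading, non-serious events are recorded for about 4% to 50% of the time from first session to 6 months, and not at all in controls. The clock starts at the first session because time from discharge can include weeks before consent and randomisation. Appendix 2 also allows sessions on successive days, which would shorten the covered time further.

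**Sensitivity to the follow-up date**

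Section 12 and Appendix 2 place the repeat contact at 4 months (17.4 weeks; plus or minus 2 weeks in section 12). Coverage would then run from 1/17.4 = 5.7% (start week 0, 2 sessions) to complete (start week 12, 8 sessions: last session at week 19, after the nominal contact). The size therefore depends on a date that the protocol has not settled.

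**Precision**

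The one-sided 95% upper bound after zero events is 1 − 0.05^(1/n). For n = 13 it is 20.6%. The protocol's 18 to 20 completers agree with its 25% loss (26 × 0.75 = 19.5). With equal loss, 9 to 10 per arm would reach the final contact, and the bound at that contact is 28.3% (n = 9) to 25.9% (n = 10).

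**The case against.** The strongest reply is that serious harm is already covered. Section 11 puts no limit of phase or arm on SAEs, lists hospitalisation and death among the SAE criteria, and tells staff to treat as serious any event that may jeopardise the patient. A reader might infer that readmission or serious self-harm after therapy goes unrecorded. The documents do not support that: on the plain wording of the SAE sentence such events are reportable in both arms. What remains is that the preceding sentence could be read to narrow this, and that no scheduled contact asks about events.

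A second reply is that the intervention phase of the trial might be meant as a calendar period common to both arms. The text does not exclude this. The missing definition is therefore the firmest part of the point, and the exclusion of controls is the natural reading rather than a stated rule.

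Third, the criterion counts attributable events. Controls cannot have events attributable to EMDR, so a count in one arm is coherent. A reader might infer that the outcome is void for want of a comparator. It is not: control data would inform judgements of attribution, and their absence weakens those judgements without invalidating the count. With 13 per arm, control data could not separate background from treatment effects with any precision either.

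Fourth, the PCL-C and HADS are collected in both arms at baseline and follow-up, so worsening distress is partly visible by arm, although not as adverse events. This stands and narrows the gap.

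**Conclusion.** The point holds for non-serious adverse events and for the unreconciled scopes. The protocol ties recording to a phase that it does not define. On the natural reading, non-serious harm is captured only in treated patients during therapy: 1 to 7 weeks, or about 4% to 50% of the time from first session to 6 months. This assumes weekly sessions, a start at week 0 to 12 and a 6-month endpoint. It is a defect in a stated rule, not a detail left to an analysis plan, because an analysis plan cannot recover events that sites were told not to record.

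It does not show that serious events are lost or that the feasibility criterion is meaningless. It should be changed because a low count of attributable events could otherwise reflect limited recording rather than good tolerability.

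Separately, the statement in section 11 that systematic reviews found no EMDR-attributable events points to items 52-56. None of these in the reference list is a systematic review of EMDR. That is a clerical error and has no bearing on event capture.

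**What to change.** First reconcile the follow-up date: 4 months in section 12 and Appendix 2, against 6 months under Secondary outcome measures and in Figure two. Then replace the restricting sentence with text such as:

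*Adverse events and serious adverse events will be recorded in both arms from randomisation to the final follow-up assessment. The same adverse-event questions will be asked in both arms at that contact. Events reported by therapists in the intervention arm will also be recorded and shown separately. Events will be tabulated by arm and by judged relatedness.*

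Add an adverse-event row to Figure two. Start the 24-hour SAE reporting clock when the research team becomes aware of the event. Correct the citation at the same time.

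The cost is protocol wording, one adverse-event page at an existing contact and slightly more data entry. Two limits remain. Contact during therapy gives treated patients more chances to report, which is why therapist reports are kept apart from answers at the common contact. Patients lost before that contact will not be asked. The gain is a defined window and like-for-like ascertainment; precision stays low.
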